### Safety issue

Adverse events:

- the number of patients not reaching tolerance to oral feeding within 7 days after surgery- the number of patients needing insulin therapy.- the number of patients requiring electrolyte corrections.

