### Inclusion criteria

- Patients must be willing to participate in the study and able to provide written informed consent form prior to any study activity.- Preoperative normal renal function, blood electrolytes (sodium, potassium, chlorite) and coagulation tests (PT, PTT).

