### Procedures common to both arms

Patients of both groups will be treated according to the ERAS Society guidelines for perioperative care for PD (Table 1) (8). Blood glucose ≥180 mg/dl will be treated with insulin injection (either subcutaneous or by continuous IV infusion). Open PD technique will be chosen by the participating centers according to their standards.

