### Study plan

Study plan and schedule of assessment are summarized in Table 2.

**Table 2 tab2:** Study plan and schedule of assessment.

Visit	V pre	V1	V2		V3	V4	In hosp FU	Dis	FU
Time interval	Pre random	Basal at random	Intraoperative	Day 1	Day 3	Day 5	Once a day during index hospitalization	Discharge	3-mo. follow-up (from the day of surgery)
Informed consent	X								
Demographics	X								
Height	X								
Weight	X							X	X
Body mass index	X								
Physical examination (every day until discharge)	X			X	X	X	X	X	X
Patient history	X								
Inclusion criteria		X							
Exclusion criteria		X							
Blood pressure		X	X		X	X	X		
Heart rate		X	X		X	X	X		
ECG		X							
ICU admission							X		
Lab tests*		X		X	X	X	X	X	
Need of insulin			X	X	X	X	X	X	X
NRS-2002		X							
Death			X	X	X	X	X	X	X
Safety endpoints				X	X	X	X	X	X
Blood loss			X						
Duration of surgery			X						
Surgical details			X						
Fluid balance			X	X	X	X	X		
Histology			X					X	
Analgesia			X	X	X	X		X	
Discharge criteria						X	X		
Complications (CCI)				X	X	X	X	X	X
Drug administration (DAY 1-5)				X	X	X			

*Urea, Creatinine, Complete blood count, PT, PTT, Glucose, Na, K, Cl, prealbumin, albumin, glycate haemoglobin, bilirubin, CRP.

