#### H1 hypothesis

The administration of a parenteral nutrition added to the ERAS protocol will positively affect the CCI as compared to standard of care (ERAS).

Secondary outcome measures will be:

- Actual daily calories delivered by PN.- Rate of unplanned artificial nutrition (for control group).- Rate and severity of complications at 90 days after discharge.- Rate of surgical site infections (16)- The rate and severity of postoperative pancreatic fistula (17)- Rate and severity of DGE (18)- Rate and severity of hemorrhage (19)- Length of stay (LOS) based on predefined criteria- Actual LOS- Rate of reoperation.- Rate and duration of intensive care treatment.- Rate of hyperglycemia (blood glucose >180 mg/dl)- Use of insulin (subcutaneous bolus or continuous infusion)- Δ plasma prealbumin levels (baseline, postoperative day 1 and 6)- Use of morphine- Readmission rate- Body weight (90 days)- 90-day mortality

Any attending surgeon will decide the day of discharge according to his individual clinical judgement. However, LOS will be also calculated by the achievement of pre-specified discharge criteria (full patient mobilization, pain controlled by oral therapy, full tolerance to oral feeding). In particular, a visual analog pain scale ≤2 must be achieved for safety discharge.

Post-discharge follow-up will be accomplished by weekly outpatient visits. Also telephone interviews will be allowed to monitor patient health state, but in case of warning signs or symptoms of a complication, patients will be asked to refer to the hospital where the operation was performed for further clinical evaluation.

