### Case report form

The following baseline patient-related parameters will be recorded:

- Age (years)- Sex- Weight (kg)- Height (m)- Body mass index (kg/m^2^)- Nutritional risk score-2002- Percent of weight loss in the 6 months prior to surgery- Charlson comorbidity index- Diabetes- Jaundice- Biliary stenting- Routine laboratory test (albumin, preabumin, bilirubin, hemoglobin, creatinine, HbA1c, CRP)- Primary disease with indication to surgical resection- ASA score- Neoadjuvant treatments

The following intraoperative parameters and events will be recorded:

- The day of operation- Type of surgical procedure (PPPD, Whipple)- Type of pancreatic anastomosis (gastric, jejunal)- The level of intraoperative contamination (clean; clean-contaminated; contaminated; dirty)- Use of epidural analgesia, TAP block, subfascial catheter- Intraoperative hypothermia (defined as body temperature < 35.5°C for more than 30 min)- Estimated blood loss (mL)- Volume of IV fluid infusion- Intraoperative blood transfusion- Fluid balance (in and out difference)- Duration of operation (minute)- Main pancreatic duct diameter- Pancreas texture (soft, intermediate, hard)- Fistula risk score

After the operation the following parameters and events will be recorded:

- Capillary blood glucose levels (every 6 h for 5 consecutive days)- Any administration of insulin (for blood glucose ≥180 mg/dL)- Occurrence of a complication (90-days)- Type of complication- The complication burden according to CCI (90-day)- The severity of complication according to Clavien-Dindo classification- The need of reoperation, reason and postoperative day- The need of unplanned intensive care treatment and the duration (days)- The day of canalization to gas and stools- The day of resumption of oral feeding- The need and duration of artificial nutrition (for the control arm)- Potential hospital discharge according to predefined criteria- The actual day of hospital discharge- Disease staging- Readmission rate (30-day)- Mortality rate (90-day)

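### The insulin safety count has no single definition, no post-randomisation start and no account of baseline diabetes or prior insulin, so its relative risk is attenuated by an unknown amount

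*Protocol article*

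**What the plan says.** Insulin appears in five places in the protocol article.

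- **Safety issue:** one of three listed adverse events is "the number of patients needing insulin therapy".
- **Secondary outcomes (under H1 hypothesis):** "Use of insulin (subcutaneous bolus or continuous infusion". A separate outcome is "Rate of hyperglycemia (blood glucose >180 mg/dl".
- **Case report form, postoperative items:** "Any administration of insulin (for blood glucose ≥180 mg/dL", next to "Capillary blood glucose levels (every 6 h for 5 consecutive days".
- **Procedures common to both arms:** "Blood glucose ≥180 mg/dl will be treated with insulin injection".
- **Study plan, Table 2:** the row "Need of insulin" has no mark at the pre-randomisation visit or at V1. Its first mark is intraoperative, and its last is at the 3-month follow-up.

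On eligibility, the inclusion criteria ask for "Preoperative normal renal function, blood electrolytes (sodium, potassium, chlorite) and coagulation tests (PT, PTT" and set no glycaemic condition. The exclusion criteria mention neither diabetes nor insulin. Diabetes and HbA1c are baseline items on the case report form, and diabetes is a pre-specified subgroup factor, but only for the effect on the Comprehensive Complication Index (CCI). Preoperative insulin treatment is not a listed item. Binary endpoints are to be compared by relative risk with a 95% confidence interval and the Fisher test (Statistical planning).

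**The concern.** Parenteral nutrition delivers carbohydrate, so insulin need is a natural place to look for metabolic harm. A useful count would isolate need that arises after treatment could have acted. The two outcome entries do not do this, for three reasons.

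1. They omit the glucose condition that the case report form attaches to the same variable, so it is unclear which insulin counts.
2. They set no start time. Table 2 first records insulin during surgery, which is before allocation and before parenteral nutrition.
3. They pool patients with and without diabetes, and prior users with non-users.

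Patients likely to need insulin whatever their arm enter both numerators. For a harm outcome summarised as a relative risk, that moves the estimate towards no difference and makes a real effect harder to see.

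**Working it through.** **Sequence of events.** Screening and randomization processes places allocation at 8 PM on the day of surgery, or 8 AM on postoperative day 1 if surgery ends after 8 PM. Study intervention starts parenteral nutrition on postoperative day 1. The intraoperative insulin entry therefore precedes both. The column order of Table 2 puts the visit at randomisation before the intraoperative visit, but the text gives the clock times. On either reading, the entry precedes parenteral nutrition.

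**Wording side by side.** The case report form and the common treatment rule tie insulin to glucose at or above 180 mg/dL. The adverse event and the secondary outcome do not. Capillary glucose is listed for 5 days, while Table 2 records insulin need up to 3 months. The later entries thus have no listed 6-hourly glucose series behind them. The hyperglycaemia outcome uses a strict inequality (>180), so a reading of exactly 180 would call for insulin without counting as hyperglycaemia.

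**Size of the attenuation.** The plan states no insulin rate, so there is no figure to reproduce. Its sample size concerns the CCI and is used here only for the number of patients: 120 × (1 − 0.10) = 108 evaluable per arm.

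Assumptions, none from the documents: a share p uses insulin before surgery, every prior user is an event in both arms, and new need among non-users is c in control and t with parenteral nutrition.

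- Observed rate in an arm = p + (1 − p) × new-need rate
- Relative risk (RR) as written = [p + (1 − p)t] / [p + (1 − p)c]
- Risk difference as written = (1 − p)(t − c)

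With c = 0.20 and t = 0.40:

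| p | Control | Parenteral nutrition | RR | Risk difference | Power, all 108 | Power, non-users only |
|---|---|---|---|---|---|---|
| 0 | 0.20 | 0.40 | 2.00 | 0.20 | 0.90 | 0.90 |
| 5% | 0.24 | 0.43 | 1.79 | 0.19 | 0.85 | 0.88 |
| 10% | 0.28 | 0.46 | 1.64 | 0.18 | 0.79 | 0.87 |
| 20% | 0.36 | 0.52 | 1.44 | 0.16 | 0.66 | 0.82 |

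Power is from the normal approximation for two proportions at two-sided 5%, with 108(1 − p) per arm for non-users.

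With c = 0.30 and t = 0.50, an RR of 1.67 becomes 1.57, 1.49 and 1.36 at p = 5%, 10% and 20%.

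**Why this is an upper bound.** Let prior users be events with probability q, the same in both arms. Then RR = [pq + (1 − p)t] / [pq + (1 − p)c]. At p = 10% with 20% against 40%, q = 1 gives 0.46/0.28 = 1.64 and q = 0 gives 0.36/0.18 = 2.00. Any q in between lies between these. Under the case report form wording, prior users given usual insulin below the threshold are not events, so q is below 1.

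**Excess number of patients.** At p = 10%, the expected excess among all 108 is 108 × (0.46 − 0.28) = 19.44. Among the 108 × 0.90 = 97.2 non-users it is 97.2 × (0.40 − 0.20) = 19.44. The two are identical.

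**The case against.** A reader might infer that anyone on insulin before surgery is a certain event in both arms, so that the count hides the main metabolic harm of parenteral nutrition, including from the data and safety monitoring board. The documents do not support that, for these reasons:

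- The case report form item is glucose-triggered, so a prior user is not automatically an event.
- Randomisation balances prior users in expectation, and the excess in affected patients is unchanged, as shown above. The loss is on the ratio scale and in precision.
- Hyperglycaemia is a separate outcome with readings every 6 hours over the planned parenteral nutrition period.
- Recorded diabetes and HbA1c would allow most of the separation, and the patient history taken at the first visit may hold prior treatment.
- No stopping rule uses insulin counts.

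It can also be said that a medication field and a finer event definition belong in the full protocol or analysis plan, which are not shown.

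The first five points stand, and they limit the size of the problem. The last stands only in part. The article does state its definitions, and they differ: two outcome entries lack the condition that the case report form carries, and the schedule begins before allocation. The recorded diabetes status is assigned only to the CCI subgroup analysis. Hyperglycaemia is not among the three adverse events, and its outcome entry does not refer to baseline diabetes either.

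**Conclusion.** The point holds as a loss of sharpness in a safety comparison. As worded, the insulin adverse event and secondary outcome mix need that may follow from parenteral nutrition with need that would occur anyway, and they differ from the recorded variable. The planned relative risk is attenuated and some power is lost.

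The amount cannot be fixed from the documents, because neither the share of prior users nor any insulin rate is given. At most, for assumed new need of 20% against 40%, a relative risk of 2.0 would read between 1.79 and 1.44 for prior use of 5% to 20%. This bound assumes that parenteral nutrition does not lower insulin need in prior users. Insulin given during surgery to non-users would add to the dilution if it were counted; the article does not say whether it is.

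The eligibility of prior users follows from the absence of any exclusion, not from an explicit statement. The primary endpoint and the stopping rules are unaffected.

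**What to change.** 1. Use one definition of the insulin event in Safety issue, the secondary outcomes and the case report form, so that the analysed variable is the recorded one. Reconcile the ≥180 and >180 wording at the same time.
2. Count insulin started after randomisation. Keep the intraoperative entry as a descriptive, pre-treatment variable.
3. Report the insulin and hyperglycaemia comparisons by baseline diabetes status, or adjusted for it. It is already collected and is not a stratification factor.
4. Add one baseline item for preoperative insulin. Report new need in non-users separately from increased need in prior users, since resuming a usual regimen after surgery would otherwise look like a new start.
5. Give the risk difference or the excess number of patients beside the relative risk, because that count is not affected by the dilution.

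The cost is one case report form item, some rewording and a slightly smaller denominator for the new-need event. Under the 20% against 40% example at 10% prior use, restricting to non-users raises power from 0.79 to 0.87 despite the smaller number. No clinical rule changes.

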## Statistical planning

The sample size of 120 patients per group is necessary to provide an 80% power to detect at least a 30% reduction in the CCI, which is expected to be around 23 (median) (IQR 21–31) or mean 27 (±20 SD) in complicated patients of the control group. The hypothesized reduction of 30% is based on sound clinical relevance meaning that such reduction will have a consistent and significant impact of the postoperative course with advantages on well-being, quality of life, shorter length of hospitalization and a relevant reduction of heath care burden and resources. The median CCI of 23 is retrieved from a previous publication (20). The rate of complication in this type of surgery is expected to be approximately of 60%.

A Mann–Whitney test is considered, type I error rate is fixed at 5% (two tails) and an expected drop-out of 10% is taken into account.

For the binary end-points, the relative risk (RR) with the corresponding 95% confidence interval, comparing the two groups, will be estimated. For the primary end-point, also the risk difference (RD) will be computed. For the numerical end-points the difference in the location parameter (i.e., median pairwise difference) between the two groups with the corresponding 95% confidence interval will be computed. Fisher test and Mann–Whitney test will be adopted to evaluate univariate associations. Incidence of complications over time in the two groups will be described according to the Nelson-Aalen cumulative hazard estimator also accounting for multiple events per patient. The incidence in the two groups will also be compared by computing the incidence rate ratio (with 95% confidence interval). This analysis will be performed both considering all complications and only major complications.

A multivariate quantile regression model (focused on median, 25^th^ and 75^th^ percentiles) will be used to identify factors associated with the primary endpoint and to evaluate the effect of treatment adjusting for possible residual confounding. Logistic regression will also be used to model the probability of CCI >23. Using these regression models, the effect of PN over controls on the CCI will be also investigated within pre-specified subgroups to account for possible effect modification. The pre-specified risk factors for this analysis will be:

- Nutritional risk screeing-2002 (≥3)- Body mass index (> 30)- Sex (male)- Age (>70 years)- Charlson comorbidity index (>4)- ASA score (=3)- Blood loss (≥500 mL)- Duration of surgery (>360 min)- Biliary stenting- Diabetes- Pylorus-preserving PD (vs. Whipple)- Pancreatic ductal carcinoma (vs. others)- Fistula risk score (≥7)- ERAS overall compliance (>70%)

All analyses will be done based on the principles of “intention-to-treat” and “per-protocol” and performed with the R software.

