## Outcomes

The primary endpoint of the trial is the complication burden within 90 days after surgery. The complication burden will be assessed by the Comprehensive Complication Index (CCI) (15), that incorporates all complications and their severity as defined by the Clavien-Dindo classification, and summarizes postoperative morbidity with a numerical scale ranging from 0 (no complication) to 100 (death).

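### The stated 80% power for 120 patients per group is not supported for the primary test once the roughly 40% of patients expected to score CCI 0 are counted

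*Protocol article*

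**What the plan says.** All references are to the protocol article.

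- Statistical planning claims that "The sample size of 120 patients per group is necessary to provide an 80% power to detect at least a 30% reduction in the CCI". The test is Mann–Whitney, two-sided at 5%, with 10% drop-out allowed for.
- The control-group CCI is taken as "around 23 (median) (IQR 21–31) or mean 27 (±20 SD) in complicated patients of the control group".
- The next lines add: "The rate of complication in this type of surgery is expected to be approximately of 60" per cent. The article does not show how this rate enters the calculation.
- Under Outcomes, the primary endpoint is the CCI, which "summarizes postoperative morbidity with a numerical scale ranging from 0 (no complication) to 100 (death").
- On the analysis set, the end of Statistical planning begins "All analyses will be done based on the principles of" and names intention-to-treat and per-protocol. Nothing limits the primary comparison to patients with a complication.

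**The concern.** The planning values describe one population and the primary test uses another. The mean, SD, median and quartiles belong to patients who had a complication. The test compares all randomised patients, about 40% of whom are expected to score exactly 0 in the control arm. Adding them lowers the mean, so a 30% reduction is fewer CCI points. It also puts a large block of ties into the rank test.

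Readers will judge a null result against the stated power. If the real figure is lower, a non-significant comparison will be taken as stronger evidence against a 30% reduction than it is.

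**Working it through.** **Inputs.** From Statistical planning: 120 per group, 80% power, 30% reduction, mean 27, SD 20, quartiles 21/23/31 (complicated patients), 60% complicated, two-sided 5%, Mann–Whitney, 10% drop-out. From Outcomes: no complication scores 0. Evaluable per arm: 120 × 0.9 = 108.

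**Step 1: reproduce the plan's figure.** Apply the complicated-patient values to everyone. The difference is 0.30 × 27 = 8.1.

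- n = 2 × (1.96 + 0.8416)² × (20/8.1)² = 95.7 per arm.
- With the worst-case Mann–Whitney efficiency: 95.7/0.864 = 110.8. Drop-out then gives 110.8 × 1.1 = 121.8, or 110.8/0.9 = 123.1.
- With a 15% non-parametric inflation: 95.7 × 1.15 × 1.1 = 121.1.
- With efficiency 0.955: 95.7/0.955 = 100.2, rounded up to 101; 101/0.9 = 112.2, so 113.
- Power at 108 per arm: 79.0% (efficiency 0.864) or 82.9% (0.955).

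So 120 per group and 80% are roughly what results if every patient is given mean 27 and SD 20.

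**Step 2: put the 60% in.**

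- Control mean over all patients: 0.6 × 27 = 16.2.
- Variance: 0.6 × (20² + 27²) − 16.2² = 677.4 − 262.4 = 415, so SD 20.4.
- A 30% reduction is 0.30 × 16.2 = 4.86 points instead of 8.1, with almost the same spread.

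**Step 3: power of the planned test.** Two-sided Mann–Whitney, 108 per arm, control arm 60% complicated and 40% at 0, 1,500 or more simulated trials per scenario. Each scenario lowers mean CCI by 30%. Severity only multiplies complicated patients' scores by 0.7. Rate only lowers 60% to 42%. The even split uses 60% to 50.2% and a factor of 0.837 (0.502 × 0.837/0.6 = 0.70).

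| CCI shape in complicated patients | Severity only | Even split | Rate only |
|---|---|---|---|
| Gamma or lognormal, mean 27, SD 20 | about 20–30% | about 43–49% | about 67–71% |
| Quartiles 21/23/31, SD about 17–20 | about 54–77% | about 60–72% | about 67–71% |

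One quartile shape whose lower tail ran down to 1 fell below its row (43–44%, severity only). Shapes with the same quartiles but SD about 9–12 exceeded 80% (up to 87%, severity only).

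**Step 4: shapes that meet all the stated values.** As a check I built shapes with mean, SD and quartiles all close to the plan's. In one, the four quarters are uniform on 1–21, 21–23 and 23–31, and then 76% at 31 with 24% at 100.

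- Mean: (11 + 22 + 27 + 47.56)/4 = 26.9.
- Mean square: (154.3 + 484.3 + 734.3 + 3130.4)/4 = 1125.8, so SD = √(1125.8 − 26.89²) = 20.1.

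This shape and two variants gave 69–75% (severity only), 68–69% (rate only) and 72–79% (even split).

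**The case against.** The strongest reply has four parts.

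1. **The 60% may have been used.** The article prints no formula and condenses a fuller protocol. Complicated-only routes also reach 120: 72/0.6 = 120 (unequal SDs 20 and 14, no drop-out), or 65/0.6/0.9 = 120.4. This stands: a reader might infer that the rate was ignored, but the document does not show that. Either route would power a comparison of a subset defined after randomisation, not the all-patient test, so the claim for the primary test remains unsupported.

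2. **80% does not require every patient to have a complication.** A reader might infer that from Step 1. It is not so: with the lognormal shape and severity only, power at 108 per arm is still about 87% at a 90% complication rate.

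3. **The planned test is a rank test and the quartiles are tight.** This stands in part. A reader might infer that the trial would more likely than not miss a 30% reduction. The documents do not support that: most quartile-preserving shapes and nearly all rate-only scenarios exceed 50%. The two-means formula with Step 2's values gives about 42%, but that is not the planned test and I do not rely on it.

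4. **Some shapes come close to 80%.** With quartiles 21/23/31, lowest score 15 and 6% at 100, one version (SD 19) gave 76% at 108 per arm and 82% at 120 without drop-out. In my check, another (SD 18.8) gave 81% at 108, but its mean was 29.1 rather than 27. The boundary is therefore not sharp.

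That an analysis plan may exist does not answer the point. The article itself makes the power claim and gives the inputs.

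**Conclusion.** The point holds as a wrong figure: 80% power with 120 per group does not follow for the primary test on all randomised patients from the plan's own inputs. At 108 evaluable per arm the Mann–Whitney power is about 20–30%, 54–77% or 67–71%, depending on the CCI shape and on whether severity or rate falls. Shapes meeting the stated mean, SD and quartiles together gave roughly 68–79%. Reaching 80% at that size takes a distribution tighter than the stated SD 20 allows, apart from the borderline shape noted above, which misses the stated mean.

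The result rests on the expected 60% complication rate, 10% drop-out, a 30% fall in mean CCI over all patients, and assumed shapes and rate/severity splits that the article does not give. The direction of the error is clear on the stated mean and SD. Its size is not, and could be small or large.

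**What to change.** Recompute power by simulating the Mann–Whitney test on all randomised patients, with the expected 40% at CCI 0. Use one distribution for complicated patients that is compatible with both the mean/SD and the median/IQR, or say which pair is withdrawn. State how much of the 30% reduction comes from fewer complications and how much from lower severity, and show where the 60% and the 10% drop-out enter. Then replace the 80% with the resulting power, or with the reduction detectable at 80% power with 120 per group.

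The sample size, endpoint and test need not change. The cost is a rewritten sample-size paragraph and a less favourable stated power.

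### With about 40% of patients expected at CCI 0, the median pairwise difference can report a real benefit as 0.0 and the 25th-percentile regression is uninformative; the risk difference has no named binary form

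*Protocol article*

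**What the plan says.** The Outcomes section defines the primary endpoint as the Comprehensive Complication Index within 90 days, on a "numerical scale ranging from 0 (no complication) to 100 (death"). Under Statistical planning:

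- "The rate of complication in this type of surgery is expected to be approximately of 60" percent.
- The trial is sized for "80% power to detect at least a 30% reduction in the CCI". The planning values behind this (median 23 with quartiles 21 and 31, or mean 27 with SD 20) describe only those control patients who have a complication.
- The primary test is a two-sided Mann–Whitney test. For numerical endpoints, "the difference in the location parameter (i.e., median pairwise difference) between the two groups with the corresponding 95% confidence interval will be computed".
- "For the primary end-point, also the risk difference (RD) will be computed". The sentence names no binary version of the CCI.
- Adjusted analysis and subgroup work use "A multivariate quantile regression model (focused on median, 25^th^ and 75^th^ percentiles") and a logistic model for CCI >23. An incidence rate ratio compares the number of complications.

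**The concern.** A patient without complications scores 0, so a 60% complication rate leaves about 40% of patients tied at one value. The CCI figures used for planning describe complicated patients only and do not show this block of zeros.

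The median pairwise difference is the only between-arm estimate with a confidence interval that the article names for numerical endpoints. It would therefore normally be read beside the primary test. With so many ties it can be exactly 0 when one arm is truly better. A reader could then see a significant p-value beside an effect of 0.0, or a real benefit summarised as none.

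A 25th percentile that lies inside the zeros in both arms cannot show a treatment effect. A risk difference needs a yes/no outcome. If none is named, the cut-point can be chosen after the data are seen.

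**Working it through.** **Inputs from the article.** 120 per group; 10% drop-out, so 120 × 0.9 = 108 evaluable; two-sided 5%; 80% power; 30% reduction; complicated controls with median 23 (IQR 21–31) or mean 27 (SD 20); complication rate 60%; no complication = 0.

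**Assumptions (not in the article).** The CCI shape among complicated patients, and how the 30% arises. Three routes were tried:
- severity × 0.7 at an unchanged 60% rate;
- rate and severity each × √0.7 = 0.837, so the rate is about 50%;
- rate cut from 60% to 42%, severity unchanged.

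**Step 1: the plan's own figure.** The difference is 0.30 × 27 = 8.1. Per arm, n = 2(1.96 + 0.842)² × 20² / 8.1² = 95.7, or 96. Dividing by the lower-bound Mann–Whitney efficiency, 95.7/0.864 = 110.8. For drop-out, 110.8/0.9 = 123.1 or 110.8 × 1.1 = 121.8, both within 3% of 120. The match requires giving every patient the mean and SD of complicated patients, so the zeros do not enter.

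**Step 2: true median pairwise difference.** Let D be the CCI of a PN patient minus that of a control patient, and p the chance that a complicated PN patient scores lower than a complicated control.

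Severity-only benefit:
- P(D = 0) = 0.4 × 0.4 = 0.16
- P(D < 0) = 0.6 × 0.4 + 0.6 × 0.6 × p = 0.24 + 0.36p
- The median of D is below 0 only if 0.24 + 0.36p > 0.5, that is p > 0.26/0.36 = 0.722.

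Lognormal with mean 27/SD 20: p = 0.649 and P(D < 0) = 0.473, so P(D ≤ 0) = 0.633 and the median is exactly 0. Shapes with quartiles 21/23/31: p is about 0.74 and P(D < 0) about 0.508, so the median is just below 0.

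Rate-only benefit: P(D < 0) = 0.6 × 0.58 + 0.6 × 0.42 × 0.5 = 0.474 and P(D = 0) = 0.4 × 0.58 = 0.232. The median is 0.

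Over five shapes and three routes, the true value is 0 in 13 of 15 scenarios.

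**Step 3: simulated trials** (2,000 per scenario, at 108 and at 120 per arm).

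| Source of the 30% benefit | Estimate exactly 0 | p < 0.05 and estimate exactly 0 |
|---|---|---|
| Severity only | 42–80% | 4–13% |
| Rate and severity | 57–78% | 21–31% |
| Rate only | 71–76% | 40–48% |

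Within the severity-only row, the estimate is exactly 0 in 73–80% of trials for a lognormal or gamma with mean 27/SD 20, 51–53% for a lognormal with median 23 and 75th percentile 31, and 42–44% for shapes with quartiles 21/23/31. Positive scores were treated as continuous. Grouping them in steps of 4, an arbitrary choice to mimic ties, raised the share in every scenario tried.

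**Step 4: 25th percentile.** It is 0 in an arm when more than a quarter of its patients score 0. With a 40% chance of 0 the binomial probability is 0.9992 at n = 108 and 0.9996 at n = 120. In the simulations both arms were at 0 in at least 99.8% of trials.

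**Step 5: median.** With the PN complication rate at 60%, the PN-arm median is 0 in only about 1–2% of trials (binomial, n = 108). At a rate of about 50% it is 0 in about 45%, and at 42% in about 94%.

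**Step 6: a tie-aware measure in the same scenarios.** P(D < 0) + ½P(D = 0), where 0.5 means no effect:
- severity only, lognormal: 0.473 + 0.080 = 0.553
- severity only, quartile-matched: 0.508 + 0.080 = 0.588
- rate only: 0.474 + 0.116 = 0.590

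It shows the benefit where the median pairwise difference is 0 or just below.

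**The case against.** The strongest reply has four parts.

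1. The median pairwise difference is well defined without a shift model, and the article defines it that way and adds a confidence interval. With ties it is coarse, not invalid. This stands: the fault is that it informs poorly, not that it does not exist.

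2. A reader might infer that the estimate is exactly 0 in most trials. The document does not support that as a general statement. With its own quartiles and a severity-only benefit the share is 42–44%, and the true value is slightly below 0. The mean 27/SD 20 fits that give 73–80% are an assumed shape; the lognormal's simulated quartiles (about 14/22/34) differ from the stated IQR of 21–31.

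3. A reader might also infer that the planned effect measures fail as a group, or that two of the three quantile models are degenerate. Neither follows. The Mann–Whitney test handles ties, and the 75th-percentile model, the logistic model for CCI >23 and the incidence rate ratio do not depend on these points. The median model is unstable only if the PN complication rate drops to about 50% or below, and the article never states such a drop. Even the 25th percentile could exceed 0 in covariate strata where more than 75% of patients have complications.

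4. The risk-difference sentence follows the one on binary endpoints, and CCI >23 is already used in the logistic model. An analysis plan not shown may name the binary form. This makes it an ambiguity rather than an error, and the weakest of the three points.

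What the reply does not remove: the article itself chooses the median pairwise difference and the 25th percentile, and its own complication rate makes the first often 0 and the second almost always 0.

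**Conclusion.** The concern holds in limited form. That about 40% of patients sit at CCI 0 follows directly from the article. Under the planned benefit the median pairwise difference is exactly 0 in roughly 40–80% of trials, and a significant test appears beside an estimate of 0.0 in roughly 4–48%. Both ranges rest on the assumed shapes and on the three assumed routes to a 30% benefit.

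The uninformative 25th-percentile model needs only the 60% rate (over 99% of trials, unadjusted). The risk difference needs a named outcome. The test of H0 remains valid with ties. What is at risk is how the size of the effect is estimated and reported.

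**What to change.** Settle these before outcome data are seen by arm:

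- Beside the primary test, report the Mann–Whitney probability (or win odds), ties counted half, with a 95% CI. Add the difference in mean CCI with a bootstrap CI as support. Its drawback is sensitivity to deaths, which score 100.
- Replace the 25th-percentile regression with a proportional-odds (ordinal) model of the CCI as the adjusted analysis. Keep the median and 75th-percentile models as support; dropping the median model would be a matter of preference.
- Tie the risk difference to a named binary outcome, such as CCI >23, which the plan already uses, or any complication.

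The cost is analysis wording and code. No extra patients or data are needed, and the primary test does not change.
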